### 5.4 INTENDED PURPOSE OF THE IP IN THE PROPOSED CLINICAL INVESTIGATION

The intended use of ColdZyme® Mouth Spray (according to the IB, 2018):

- It can reduce the probability of catching a cold
- it can help shorten the duration of a cold if used at an early stage of the infection.

The present study focuses on generating clinical data with respect to cold symptoms when ColdZyme® (CMS008618) is used at an early stage of the infection.

### 5.5 POPULATIONS AND INDICATIONS FOR WHICH THE IP IS INTENDED

The indication for ColdZyme® Mouth Spray (according to the IB, 2018):

- To be used when exposed to cold viruses or early on when cold symptoms occur; it is suitable for adults and children over 4 years.

## 5.6 INSTRUCTION FOR USE

The IP should be applied every second hour up to 6 times, with each time 2 sprays (1 dose) per occasion. The user should open the mouth, aim the nozzle towards the throat, press on the pump and spray 2 times per occasion.

Figure 1: Application of spray

## 6 LITERATURE REVIEW

### 6.1 PRECLINICAL TESTING

In a recent non-clinical study (Stefansson et al, 2017), it was demonstrated that ColdZyme® Mouth Spray has a virus deactivating ability against four major common cold viruses. A virucidal efficacy suspension test was conducted using ColdZyme® Mouth Spray against each of the challenge viruses in suspension. ColdZyme® Mouth Spray deactivated rhinovirus type 1A by 91.7%, rhinovirus type 42 by 92.8%, human influenza A virus H3N2 by 96.9%, respiratory syncytial virus (RSV) by 99.9% and adenovirus type 2 by 64.5%.

A biological safety assessment has confirmed that no undue toxicological hazards are associated with the use of the materials of construction of ColdZyme® Mouth Spray and no appreciable toxicological risks are likely to arise from its intended use. The biological evaluation was conducted in accordance with relevant principles set out in ISO 10993-1:2010 and included chemical characterisation and appropriate biological tests (IB, 2018).

### 6.2 CLINICAL DATA

A recent clinical study (Clarsund et al., 2017) investigated the performance of ColdZyme® Mouth Spray in rhinovirus-inoculated healthy volunteers. This randomized, double-blind, placebo-controlled pilot study was conducted on 46 healthy volunteers inoculated with rhinovirus 16 via the nose. Subjects self-administered ColdZyme® or placebo 6 times daily for 11 days and recorded symptoms daily in a diary. Rhinovirus 16 in nasal and oropharyngeal samples at days 0, 3, 4, 6, 7 and 10 were assessed by quantitative real-time polymerase chain reaction. The primary outcome measure was the reduction in viral load in oropharyngeal samples. Exploratory analysis measuring the total viral load (i.e., area under the curve) for days 3-10 in successfully inoculated subjects found that ColdZyme® Mouth Spray treatment resulted in a lower total viral load in the oropharynx ( $p = 0.023$ ). In subjects who experienced a symptomatic common cold, treatment with ColdZyme® Mouth Spray resulted in a reduction in the number of days with common cold symptoms from 6.5 to 3.0 days ( $p = 0.014$ ) in comparison to placebo.

The safety and performance of ColdZyme® Mouth Spray was evaluated in further clinical investigations and post-marketing surveillance/user surveys, confirming that when ColdZyme® was used, colds contracted were of reduced duration and intensity (IB, 2018). The complication rate was comparable to that in a literature review of similar products.

Lastly, a recent exploratory methodological clinical study (sponsor's data on file) investigated the performance of ColdZyme® Mouth Spray in a population of 267 subjects with a common cold in real-life conditions. The subjects were randomised to two groups, the verum group receiving ColdZyme® and the "optional care only" group not receiving it. Both groups could use optional care as needed during the common cold period, comprising the following options: paracetamol (max. 2 g/day), ibuprofen

(max. 400 mg/day), sea water nose drops or nose spray as well as antibiotics (if required). The study showed significant effects of ColdZyme® Mouth Spray with respect to reduction of symptoms (both assessed by Jackson scale (Jackson et al., 1958) and the Sore/Irritated Throat Scales (Shephard et al., 2015).) and related functional impairment as rated per WURSS-21 Quality of Life subscore (Barrett et al., 2009).

With respect to use of the marketed product, a review of all complaints in the period from 2013 to January 2018 has been completed with an overall complaint rate of 0.014% and none of the complaints were judged to be reportable to authorities according to MEDDEV 2.12-1 rev8 (IB, 2018).

### 6.3 JUSTIFICATION FOR THE DESIGN OF THE CLINICAL INVESTIGATION

In accordance with the recommendations for assessment of efficacy as per the Note for Guidance on Good Clinical Practice CPMP/ICH/135/95, the study is designed as a randomized, placebo-controlled, double-blind clinical trial. A precedent randomized study (sponsor's data on file) evaluated Jackson symptom score scale, other symptom scales and WURSS-21 QoL functional parameters, and compared ColdZyme® with no treatment in naturally occurring common cold. All scales demonstrated an ability to detect a statistically significant benefit from the usage of ColdZyme® compared to no intervention, most sensitive being the WURSS-21 QoL scale. The result from this study justifies the use of WURSS-21 QoL scale as the primary endpoint in the current clinical investigation. The choice of placebo as a comparator is considered appropriate for the present study, as this is the first confirmatory clinical investigation with CMS008618 under real-life conditions.

As there is no adequate causal therapy for common cold currently available, the focus of clinical research in this indication lies in the evaluation of symptom relief (Eccles, 2005). Thus, the principal assessments in the study have been selected accordingly. Thereby, subject-reported outcomes have been chosen as the main endpoints, since they are widely acknowledged as the most relevant options of symptom rating (Eccles, 2012). The study population and the specified timepoints of assessments (including symptom records in the very early phase of the cold) are aligned with the intended use labeling of ColdZyme® Mouth Spray (IB, 2018).

## **7 RISK ASSESSMENT FOR THE INVESTIGATIONAL STUDY PRODUCT AND THE CLINICAL INVESTIGATION**

### **7.1 PROSPECTIVE CLINICAL BENEFIT**

Based on the available clinical evidence, an improvement of common cold symptoms is anticipated within the period of treatment with CMS008618 (ColdZyme® Mouth Spray).

### **7.2 ANTICIPATED ADVERSE DEVICE EFFECTS**

The essential requirements relevant for the device safety and performance have been assessed within an extensive risk management process, which incorporates biological evaluation, design, usability, production, quality and regulatory processes and clinical validation. Evaluation of the analysis combining all potential risks has concluded that the ColdZyme® Mouth Spray is free from unacceptable risk (IB, 2018). No contraindications for use of the device, other than hypersensitivity to any of the ingredients, have been identified in the risk management process. Risks have been further addressed in post-market surveillance and in post-market investigations. No new or unacceptable risks have been recorded, and no adverse events related to the use of the ColdZyme® Mouth Spray have been reported during post-market investigations. The chosen ingredients are well known and non-toxic. Trypsin, glycerol, calcium chloride, water, ethanol and menthol are listed in the “Generally Recognized As Safe” (GRAS) substance database of the U. S. Food and Drug Administration. Therefore, the device is concluded to achieve its intended purpose and fulfil essential requirements regarding safety and performance. For further details, please refer to the IB (2018).

The study subjects will be instructed on the relevant precautions applying to CMS008618 (ColdZyme® Mouth Spray), according to the IB (2018):

- It is not to be used by individuals hypersensitive/allergic to any of the ingredients
- The user should not inhale when applying the spray since this may cause transient asthma-like symptoms, such as coughing and hoarseness

### **7.3 RISK ANALYSIS**

#### **7.3.1 Product Specific Risks**

Safety of ColdZyme® Mouth Spray has been assessed during the risk management process and evaluation of the analysis combining all potential risks has concluded that ColdZyme® Mouth Spray does not impose any unacceptable risk to the user. The essential requirements relevant for ColdZyme® Mouth Spray safety have been handled according to the Risk Management process. Risks have been identified and evaluated according to the essential requirements with applicable harmonized standards, mitigated and, where applicable, controlled via verified control measures.

### **7.3.2 Risks due to Manufacturing Errors**

To mitigate the risk, the production is monitored by means of a quality management system ensuring that the quality of the manufactured product complies with the specified standards.

### **7.3.3 Risks due to Overdose**

To mitigate the risk, the dosing recommendations for the intended use of the device are derived from the clinical evaluation of the product.

### **7.3.4 Risks due to Improper Use**

There is labeling on the device packaging stating proper use and general and specific precautions including a 'use by date' statement and proper storage requirements. In the study, the subjects will be trained on proper use (please refer to section 11.3).

### **7.3.5 Risks due to Contraindications**

ColdZyme® Mouth Spray should not be used by individuals hypersensitive/allergic to any of the ingredients.

### **7.3.6 Overall risk Assessment**

According to the Risk Management Report, possible risks are acceptable due to low probability of occurrence and existence of sufficient countermeasures.

For further details, please refer to the IB (2018).

## **7.4 RISKS ASSOCIATED WITH THE PARTICIPATION IN THE CLINICAL INVESTIGATION**

All clinical assessments are standard practice in health care as applied to upper respiratory tract infections.

## **7.5 RISK-TO-BENEFIT RATIO**

The Risk Management Report confirms that all individual and cumulative risks associated with the use of this device have been adequately controlled and reduced to a level as low as possible (IB, 2018). It can be concluded that, since the current controls adequately ensure the safety of ColdZyme® Mouth Spray (CMS008618) and clinical studies have shown a beneficial effect on viral load and duration of symptoms, the risk-to-benefit-ratio in the present investigation may be considered as favourable.

## 8 OBJECTIVES OF THE CLINICAL INVESTIGATION

The aim of this double-blind, randomized, parallel-group design clinical investigation is to evaluate the efficacy of CMS008618 for common cold.

The endpoints selected to evaluate the effects of CMS008618 are based on the state-of-the-art assessments of upper respiratory tract infections.

### 8.1 PRIMARY ENDPOINT

Primary endpoint is the AUC of Wisconsin Upper Respiratory Symptom Survey (WURSS-21) Quality of Life composite subscore during first 8 days of symptoms, to be assessed in comparison between verum and placebo.

### 8.2 MAJOR SECONDARY ENDPOINTS

The following major secondary endpoints will be assessed in comparison between verum and placebo (1 is highest ranking):

1. AUC days 1-8 composite daily severity of all symptoms within the Jackson score (mean of morning and evening) (day 1 is the first day of symptom recording)
2. Exposure to any concomitant treatment (including natural health products) that may affect common cold symptoms - immune suppressants/immune stimulants, analgesics/anti-rheumatics, anti-phlogistics, antitussives/expectorants, mouth or throat therapeutics, decongestants, antibiotics, anti-histaminergic drugs, nasal drops/spray or any medication/treatment known to affect common cold symptoms - at any dose, expressed as number of days with concomitant treatment during the first 4 days for each subject (based on diary data).

### 8.3 OTHER SECONDARY ENDPOINTS

To be assessed in comparison between verum and placebo:

- AUC days 1-8 for each single WURSS-21 QoL subscore item
- AUC days 1-8 composite daily severity of all local symptoms within the Jackson score (mean of morning and evening)
- AUC days 1-8 composite daily severity of each individual symptom of the Jackson score (mean of morning and evening)
- Frequency of subjects with use of concomitant treatment (including natural health products) that may affect common cold symptoms - immune suppressants/immune stimulants, analgesics/anti-rheumatics, anti-phlogistics, antitussives/expectorants, mouth or throat therapeutics, decongestants, antibiotics, anti-histaminergic drugs, nasal drops/spray or any medication/treatment known to affect common cold symptoms - at any dose, during days 1-4 (based on diary data)

- Assessment of duration of first intense phase, expressed as number of days from start of treatment until scoring <5 in total Jackson score
- Assessment of symptom intensity, expressed as mean total Jackson score days 1-4
- Assessment of symptom sore throat per Sore Throat Scale, expressed as AUC days 1-8
- Percentage of subjects with confirmed common cold at Visit 2 (from all subjects with V2)
- Global evaluation of efficacy by subjects and investigators at study end

#### 8.4 SAFETY ENDPOINTS

The following safety endpoints will be assessed:

- Physical examination throughout the study
- Vital signs (blood pressure, pulse rate) throughout the study
- Global evaluation of tolerability by subjects and investigators at study end
- Assessment of adverse events throughout the study
- Assessment of device deficiencies at V2 and V3

## 9 DESIGN AND DURATION OF THE CLINICAL INVESTIGATION

### 9.1 DESIGN OF THE CLINICAL INVESTIGATION

The present clinical investigation is a double-blind, randomized, parallel-group design study.

[figure not shown]

Figure 2: Visit schedule

The study design has been chosen to align with established options for evaluation of common cold (e.g. Barrett et al., 2010; Eccles et al., 2010). The time period of the treatment phase is based on the experience with use of ColdZyme® Mouth Spray (CMS008618) and the typical duration of a common cold episode.

### 9.2 DURATION OF THE STUDY

The study duration for each subject is maximally 16 weeks  $\pm$  7 days (in the case of subjects showing no symptoms). Depending on the advent of a cold illness (symptom onset and consequently of V2) for each subject, an individual's overall study duration will differ.

The expected start date of this study is Q4 2018. The clinical phase of the study is expected to be completed by Q3 2019.

If the required number of subjects with cold symptoms completing V2 and V3 is not achieved in the winter season 2018/2019, recruitment would be stopped in March/April 2019 and then continued in the next winter season (2019/2020).

## 10 SELECTION OF STUDY SUBJECTS

### 10.1 NUMBER OF SUBJECTS

A total number of expectedly 600 subjects will be enrolled as eligible study participants and randomised at V1. The first 400 who start using IP upon experiencing symptoms should complete V2 and V3.

Depending on the percentage of subjects from those randomized at V1 who actually develop symptoms during the study period, the envisaged number of 600 recruited subjects may deviate from the final number of recruited subjects needed.

For reasons of practicability/logistics of recruitment, the targeted number of subjects with symptoms (attending V2 and V3) may be subject to deviations.

### 10.2 INCLUSION CRITERIA

1. Men and women
2. Age 18 to 70 years old
3. Increased risk for common cold (at least 3 self-reported occurrences of common cold within the last 12 months prior to V1) but generally in good health
4. Readiness to comply with trial procedures, including in particular:
  - Use of IP as recommended
  - Filling in diary
  - Keeping habitual life-style, including diet and physical activity level
  - No use of products that may influence the study outcome (e.g. immune suppressants/immune stimulants including natural health products, analgesics/anti-rheumatics, anti-phlogistics, anti-tussives/expectorants, mouth or throat therapeutics, decongestants, antibiotics, anti-histaminergic drugs, nasal drops/spray) during the study (except for the defined "rescue" treatment)
5. Women of child-bearing potential:
  - Have to agree to use appropriate contraception methods
  - Negative pregnancy testing (beta human chorionic gonadotropin test in urine) at V1

Participation is based upon written informed consent by the participant following written and oral information by the investigator regarding nature, purpose, consequences and possible risks of the clinical study.

### 10.3 CRITERIA FOR CONTINUATION AT V2

Subjects having Visit 2 after onset of common cold symptoms and start of IP use (according to predefined criteria) will continue study participation.

### 10.4 EXCLUSION CRITERIA

1. Known allergy or hypersensitivity to the components of the investigational product

2. History and/or presence of clinically significant condition/ disorder (self-reported), which per investigator's judgement could interfere with the results of the study or the safety of the subject, e.g.:
  - Nasal disorder (e.g. polyposis, relevant septal deviation, ulcer etc.) and/or reconstructive surgery
  - Asthma, chronic obstructive lung disease or any other acute/chronic airways disease/disorder (e.g. chronic cough of any origin)
  - Acute psychiatric disorders
  - Any other acute/chronic serious organ or systemic diseases
3. Influenza vaccination within the last 3 months prior to V1 and during the study
4. Regular use of products that may influence the study outcome (e.g. immune suppressants/immune stimulants including natural health products, analgesics/anti-rheumatics, anti-phlogistics, anti-tussives/expectorants, mouth or throat therapeutics, decongestants, antibiotics, anti-histaminergic drugs, nasal drops/spray) within the last 4 weeks prior to V1
5. Pregnancy or nursing
6. History of (in the past 12 months prior to V1) or current abuse of drugs, alcohol or medication
7. Participation in the present study of a person living in the same household as the subject
8. Inability to comply with study requirements according to investigator's judgement
9. Participation in another clinical study in the 30 days prior to V1 and during the study

#### 10.5 WOMEN OF CHILD BEARING POTENTIAL

Female subjects may not be pregnant at the time of inclusion into the study. Therefore, pregnancy testing will be performed during screening for women with child bearing potential (women of non-childbearing potential are defined as those who either have no uterus, or have undergone ligation of the fallopian tubes, or have permanent cessation of ovarian function due to ovarian failure or surgical removal of the ovaries, or are in the postmenopause as per investigator's judgement). During the informed consent process, the investigator will advise every woman with child bearing potential that she must use medically recognised contraception during the study duration. In case pregnancy occurs, the subject has to withdraw. Any pregnancy during the study must be reported in writing to the sponsor and the project manager of the CRO by the investigator within 24 hours of becoming aware of the event by sending the respective form to:

[name], PhD;

email: [contact]

[name];

email: [contact], [contact]

Any initial report must be followed up by a detailed written report.

## 11 CLINICAL INVESTIGATION TREATMENT

### 11.1 INVESTIGATIONAL STUDY PRODUCT

CMS008618 is ColdZyme® Mouth Spray, a Class I medical device (CE-marked) under Council Directive 93/42/EEC on Medical Device and MED-DEV Guidance Document 2.4/1. Rev 8, June 2010; with the following composition of the spray solution: glycerol, purified water, cod trypsin, ethanol (<1 %), calcium chloride, trometamol and menthol.

CMS008618 is a non-sterile mouth spray packaged in a primary container consisting of a 20 ml semi-transparent plastic bottle, pump, actuator (spray nozzle) and an actuator terminal cap.

### 11.2 PLACEBO

The placebo mouth spray solution has the following composition: ethanol (<1 %), menthol and water.

The placebo mouth spray is packaged in a primary container consisting of a 20 ml semi-transparent plastic bottle, pump, actuator (spray nozzle) and an actuator terminal cap.

### 11.3 DOSAGE AND USE OF IP

The IP (verum and placebo) should be applied every second hour up to 6 times per day with 2 sprays (1 dose) per dose occasion. At V1, the subject will be instructed on the use and the application demonstrated (see section 5.6).

Depending on the timepoint of treatment onset, there may be less IP applied on the first day of use.

The IP use should start when following conditions have been fulfilled:

- answering "Yes" to either of the questions in the subject daily diary: "Do you think/feel you have a cold?" or "Do you think/feel you are coming down with a cold (might be having the first signs of cold)?" AND
- A Jackson score of at least 1 in the subject's cold diary (mild = present, but not disturbing or irritating) for any symptom except headache

The IP should be used until 2 days after the subject is symptom free (=answering "No" to the question "Do you think that you are still sick with this respiratory infection?" for 2 days in a row), but not longer than 10 days in total.

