## 4 INTRODUCTION

A common cold is a self-limited viral infection of the upper respiratory tract (Tyrrell, 1996). Acute respiratory diseases are among the most frequent illnesses of all. They are almost exclusively caused by viruses and mostly show a natural history affecting all age groups, with well-known autumn/winter peaks (Wagner, 1996).

The typical progression differs in individuals, yet in all cases common cold presents a burden for the affected person's quality of life. Most commonly, adult subjects complain of a general feeling of sickness, nasal congestion, headache, rhinorrhea (runny nose), sore throat, hoarseness, cough and altered quality of sleep. In general, the symptoms reach maximal severity 2 to 3 days following infection, with an average overall duration of 7 to 10 days (Heikkinen & Jarvinen, 2003). A sore scratchy throat is most often a harbinger of the common cold appearing on the first day of illness; rhinorrhea and nasal congestion soon follow (Witek et al., 2015). A treatment used at the first sign of a cold that targets the scratchy upper pharynx and thereafter reduces throat and nasal symptoms, would be much desired.

Effective curative options are few due to the multiple virus types and the complex interaction between virus and host (Johnston, 1997; Hendley, 2008). Numerous symptomatic remedies are available over the counter, yet there is still no reliable treatment and their potential side effects may be substantial (Eccles et al., 2010). Effective solutions with minimal side effects (given the nonhazardous nature of the disorder) are required.

CMS008618 is ColdZyme® Mouth Spray, a marketed Class I medical device (Enzymatica AB, Sweden). It is to be used when exposed to cold viruses or early on when cold symptoms occur. It works by coating the lining of the mucous membrane, creating a protective barrier that acts osmotically on the cold viruses, trapping them and preventing them from binding with human cells, helping the body to remove them naturally.

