### 13.6 ASSESSMENT OF EFFICACY

#### 13.6.1 Subject Diary

In the daily subject diary, from V1 on, the subject will be asked to answer the questions "Do you think/feel you have a cold?" or "Do you think/feel you are coming down with a cold (might be having first signs of cold)?" (in the morning and in the evening).

From the first day he/she answers „Yes“ to either of the above questions, he/she will have to start filling out the cold diary instead, to:

- record the symptoms on the Jackson scale (twice daily, in the morning and in the evening)
- record the symptoms on the Sore Throat Scale (once daily, in the evening)
- fill out the Wisconsin Upper Respiratory Symptom Survey (WURSS-21) Quality of Life section (once daily, in the evening)
- answer the question "Do you think that you are still sick with this respiratory infection?" (once daily, in the evening)
- record the use of IP (once daily, in the evening)
- record the use of any concomitant treatment / remedies, specifying the time point of use
- if he/she stayed sick at home (away from work, school etc.) due to common cold.

The cold diary should be filled out until 2 days after the subject is symptom free (=answering "No" to the question "Do you think that you are still sick with this respiratory infection?" for 2 days in a row), but not longer than 10 days in total.

If the subjects, in an exceptional case, fail to continue filling out the diary immediately when being symptom free, no data for the 2 subsequent days in the diary would be considered as having no symptoms (corresponding to answering "No" to the question "Do you think that you are still sick with this respiratory infection?").

The total composite Jackson score (Jackson et al., 1958) is calculated by summing the following 8 symptom scores: sore throat, blocked nose, runny nose, cough and sneezing (local symptoms) as well as headache, malaise, and chilliness (systemic symptoms). Local composite Jackson score is derived by summing the local symptoms and systemic composite Jackson score by summing the systemic ones. Symptoms are assessed on a 4-point scale: 0 = none (symptom not present), 1 = mild (present, but not disturbing or irritating), 2 = moderate (symptoms sometimes disturbing/irritating), 3 = severe (symptoms disturbing/irritating most of the time).

The Sore Throat is a 0-10 Likert scale where 0=not sore and 10=very sore (Russo et al., 2013; Shephard et al., 2015).

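### Being symptom free is judged by no longer feeling sick, not by the Jackson score that opens the diary, so the diary behind the day 1-8 AUCs can close on day 2, 3 or 4 with symptoms still recorded

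*Protocol*

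**What the plan says.** **Starting (section 11.3; synopsis, duration of intervention).** Two conditions apply. The subject says Yes either to having a cold or to "Do you think/feel you are coming down with a cold (might be having the first signs of cold", and records "A Jackson score of at least 1 in the subject's cold diary (mild = present, but not disturbing or irritating) for any symptom except headache".

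**Stopping the spray (11.3; synopsis).** "The IP should be used until 2 days after the subject is symptom free (=answering 'No' to the question" that reads "Do you think that you are still sick with this respiratory infection", for two days in a row, with a cap of 10 days.

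**Closing the diary (13.6.1).** The wording is parallel: "The cold diary should be filled out until 2 days after the subject is symptom free (=answering 'No' to the question", again for two days in a row and capped at 10 days. The question is put every evening of the cold diary, which replaces the daily diary from the first Yes. Two blank days straight after becoming symptom free are counted as days without symptoms. No return to the daily diary and no restart is described.

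**The label (11.4).** Dosing runs for two days after symptoms stop. Feeling sick is not mentioned.

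**Visit 2 (13.2.1, 13.6.2).** Within 1-3 days of symptom start the investigator checks and re-issues the diary and examines whether the initial symptoms are still present.

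**What depends on the diary (15.9, 15.10).** The primary endpoint is the WURSS-21 QoL AUC over the first 8 days. The first major secondary endpoint is the Jackson AUC over days 1-8.

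**The concern.** Entry and exit are measured on different things. Entry asks whether one mild symptom is present, in a person who may only suspect a cold. Exit asks whether the person feels sick. Someone with a scratchy throat graded 1 can truthfully answer No to the second question on the first two evenings. The protocol then classes that person as symptom free on diary pages that still carry Jackson scores above 0.

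Sections 5.4 and 6.3 say that use and recording early in the infection are the purpose of the study, so this is not a remote corner of the population. The diary cannot tell a cold that has aborted from one that has not yet developed, because it may stop before the difference shows. At stake is whether the 8-day window of both confirmatory AUCs is observed. A SAP can say how to score unrecorded days, but it cannot recover what was never written down.

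**Working it through.** **1. Trace of the closing rule.** Take a subject with Jackson of at least 1 on days 1 and 2 who answers No on both evenings. Nothing in 11.3 or 13.6.1 refers to the Jackson score, an earlier Yes or a minimum number of days, so the condition is met on evening 2. The end of the diary then depends on how the two days are counted:

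- the two No days are themselves the two days: end of day 2, with 6 of 8 daily scores unrecorded;
- first No day plus two days: end of day 3, with 5 unrecorded;
- two No days followed by two more: end of day 4, with 4 unrecorded.

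A trapezoidal AUC over days 1-8 spans 7 intervals. The recorded part is (2-1)/7 = 14%, (3-1)/7 = 29% or (4-1)/7 = 43% of that width.

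**2. 11.3 against the label.** For the same subject, 11.3 counts two days of No as symptom free and sets the end of use from there. Under 11.4 the symptoms have not stopped, so use continues up to the cap. The two sections give different instructions.

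**3. The plan's own sample size (15.3).** Inputs: difference 33.9, SD 92.7, two-sided alpha 0.05, power 90%.

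- d = 33.9/92.7 = 0.366; p1 = Φ(0.366/√2) = 0.602.
- Noether: n per group = (1.960 + 1.282)² / [6 × (0.602 - 0.5)²] = 168.3, hence 169 as stated.
- Power at 169: Φ(√(6 × 169) × 0.102 - 1.96) = 90.1%. At 200 per arm (400 treated): 94.2%.

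The sample size reproduces and is not in question.

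**4. Illustration of the possible effect on power.** The protocol does not give the share q of subjects whose diary closes this way. Assume the same q in both arms, an AUC near 0 for these subjects, and p1 = 0.602 among the rest. Then

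P(X<Y) = (1-q)² × 0.602 + q(1-q) + 0.5q².

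- q = 5%: 0.5433 + 0.0475 + 0.0013 = 0.592. Power 83% at 169 per arm, 89% at 200.
- q = 10%: 0.4876 + 0.0900 + 0.0050 = 0.583. Power 75% at 169 per arm, 82% at 200.

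If these subjects have no AUC and leave the full analysis set (15.5), only numbers are lost: at 5% or 10%, power is 89% or 87% starting from 169 per arm, and 93% or 92% starting from 200.

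**The case against.** Several arguments on the other side have weight.

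- *A reader might infer that the start and stop rules can be met together on day 1.* They cannot. Stopping needs No on two consecutive days, and once the cold diary replaces the daily diary the start question is no longer asked. The two rules use unlinked measures; they do not hold simultaneously. This stands.
- *A reader might also infer that spray and diary end before the cold peaks.* The documents do not show this. The Introduction says "In general, the symptoms reach maximal severity 2 to 3 days following infection", which runs from infection and not from the first diary Yes. The longest count takes the diary to day 4, and on the longer counts the evening question is still asked on day 3 or 4. This stands.
- *Visit 2 is a safeguard.* It falls within 1-3 days and includes a diary check. That helps in practice, but it may come before the second No, and no written rule lets it override or reopen a closed diary. This stands in part.
- *Some of these colds really do abort.* Section 13.6.2 expects that, and a shortened cold could be a treatment effect. For such subjects a low AUC is a true outcome and nothing is lost. This stands, but the closing rule does not collect the scores that would identify them.
- *The power figures rest on assumptions.* The share comes from no document, and the scoring of later days may be settled in the SAP. If the earlier trial behind the 33.9 and 92.7 used a similar rule, the dilution may already be in the effect size. This stands.
- *The scenario is unusual.* A subject must say Yes to a cold and then twice deny still being sick. It is possible under the wording, and nothing in the documents says how common it is.

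**Conclusion.** The point holds as a defect in how being symptom free is defined. A subject with recorded Jackson symptoms can be classed as symptom free from evening 2, and the cold diary may then end on day 2, 3 or 4, leaving 4 to 6 of the 8 daily scores for both confirmatory AUCs unrecorded. How the two days are counted is ambiguous, no rule reopens the diary, and the label contradicts 11.3 for such a subject. All of this follows from the wording alone.

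The size of the effect on the trial is not established. The fall in power from 90% to 83% or 75% (from 94% to 89% or 82% at 200 per arm) is an illustration under an assumed 5% or 10% share, an assumed AUC near 0 and equal shares in both arms. The loss is smaller if these subjects leave the full analysis set or if their colds truly aborted. It should not be read as a prediction. The change is still worth making because it is cheap and the missing days cannot be recovered afterwards.

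**What to change.** **Diary (13.6.1).** Do not let the diary close on any day on which that day's Jackson score is above 0. More simply, keep the diary through day 8 for every subject, so that the AUC window is always observed. The second option also avoids having to decide whether a lone headache, which the start rule excludes, should keep the diary open. In either case, state with a worked example how the two days are counted.

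**Spray use (synopsis, 11.3, 11.4).** The sponsor must reconcile what symptom free and the label's end of symptoms mean and how the two days are counted, and use the same wording in all three places. No clinical rule is proposed here.

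**Cost.** A sentence or two in 13.6.1, matching diary instructions, and a few more diary pages for some subjects. The Jackson scores are already collected. The current version is dated May 2019 against a proposed start in Q4 2018, so some diaries may already have been completed under the present rule; if so, record which diary version each subject used.
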